## Abstract

**Background:**

Recent studies have shown that nurses have been more affected by the COVID-19 pandemic than any other group of hospital workers in terms of anxiety, depression, and burnout. Several clinical studies had previously demonstrated the effectiveness of mindfulness and compassion interventions in reducing burnout and emotional distress amongst healthcare professionals.

**Methods and analysis:**

A parallel-group randomized controlled trial will assess the feasibility, acceptability, and efficacy of a mindfulness and compassion-focused programme on frontline nurses who had been working during the COVID-19 pandemic. Seventy-two participants will be recruited from Verona University Hospital Trust (Veneto Region, north-east Italy) and will be divided equally into an intervention group and a control group. Primary outcome will be assessed using the Emotional Exhaustion subscale of the Maslach Burnout Inventory General Survey (MBI-GS). Secondary outcomes will be measured by the Cynicism and Professional Efficacy subscales of the MBI-GS, the Patient Health Questionnaire (PHQ-9), the Generalized Anxiety Disorder (GAD-7), the Insomnia Severity Index (ISI), the Impact of Stressful Events (IES-R), the Perceived Stress Scale (PSS), the Five Facet Mindfulness Questionnaire (FFMQ), and the Forms of Self-Criticising/attacking and Self-Reassuring Scale (FSCRS).

**Discussion:**

The study aims to fill a gap in the literature and present a scientifically validated intervention for those healthcare professionals most exposed to the stressful conditions of working during the COVID-19 pandemic.

**Trial registration:**

ClinicalTrials.gov; Identifier: NCT05308537

## Introduction

### Background and rationale

From the beginning of the COVID-19 pandemic, healthcare workers (HCWs) worldwide experienced overwork, increased health risks in the absence of clear guidelines, and the reorganization of their activities. These factors, combined with exposure to a condition of increased mortality and a sense of uncontrollability, have led to growing incidences of burnout, anxiety, depressive symptoms, and a reduced investment of energy in the professional sphere [1–3]. Nurses were amongst the HCWs most exposed to the negative psychological effects of the COVID-19 pandemic, particularly those working in departments most involved in the treatment of COVID-19 patients, such as intensive care, infectious disease, and pulmonary units and emergency rooms [1, 2, 4].

Currently several groups across the world are working to develop initiatives aimed at supporting the well-being of HCWs facing the psychological impacts of the COVID-19 pandemic, through easy-to-access supportive psychological services [5–7]. However, there is a lack of evidence from randomised trials testing interventions with a sound base of evidence that can inform the selection of treatments that may be beneficial to the mental health of frontline HCWs facing the current pandemic [8].

Previous research has shown the effects of certain intervention strategies in reducing burnout and emotional distress amongst HCWs in the pre-COVID 19 era. These interventions included mindfulness, stress management, and small group discussion [9–13]. Over the past 20 years, studies have shown that mindfulness-based interventions are effective in reducing stress, anxiety, depression, and obsessive disorders [14–18]. Mindfulness can be defined as an awareness of present-moment thoughts, feelings, and bodily sensations through intentional and non-judgemental attention [19]. It is a state of consciousness that allows the mind and body to build a relationship of harmony and balance, a predisposing element for the condition of well-being [14]. The most scientific mindfulness-based interventions, such as MBSR (mindfulness-based stress reduction) [19] and MBCT (mindfulness-based cognitive therapy) [20] consist of weekly group meetings of 2 h and 30 min for a period of 8 weeks, with an intensive day in the middle of the programme.

Studies investigating the diffusion of clinical models based on mindfulness have allowed us to hypothesize that it can play an important role in emotional self-regulation [21]. It can, therefore, be argued that mindfulness allows one to reduce suffering and create a healthy mind by using self-processing processes [22] and modulating awareness of self and one’s emotional states and behaviours, as well as relationships with others. The ability to manage suffering, for example of patients and caregivers, stems from an empathic and emotional attunement known as compassion to the suffering of another person [23]. Compassion can be defined as the awareness of one’s own and others’ suffering and the intention or motivation to alleviate it [24]. It has been associated with the capacity to adjust to distressful experiences during dramatic events such as pandemics [25, 26] and amongst HCWs in particular [27, 28]. From this compassion-focused point of view, the distress a HCW may experience may be targeted and reduced by balancing the capacity to be compassionate with the others together with the capacity to receive compassion from oneself and others [25, 29]. This theoretical stance is consistent with the clinical practice of supporting HCWs in finding a sustainable work-life balance, promoting teamwork and valuing their professional commitment in caring their patients.

Compassion arises when an individual feels a deep connection to the suffering of others [30]. It facilitates emotional regulation, psychological flexibility and promotes relational and ethical skills [22, 30, 31]. Several studies have indicated that efficacious results can be achieved through 4-week or 6-week programmes [32–34]. These seem to be equally effective as longer programmes in terms of reducing burnout and improving the well-being and quality of life of HCWs. They are also more easily implemented in organizational settings, are less costly, and have a higher likelihood of participation and a lower risk of dropout [18].

Studies evaluating the efficacy of mindfulness amongst HCWs working during the current COVID-19 pandemic are rare, though some are in progress [11]. Results from mindfulness protocols lead us to hypothesize that such interventions may be a valuable therapeutic tool for HCWs who are working under pandemic conditions and are at risk of experiencing burnout and psychological problems. The present project is based on the results of a longitudinal study that assessed the psychological impact of the COVID-19 pandemic on HCWs at the Verona University Hospital Trust during the lockdown phase (March-May 2020) and after 1 year later [2, 4]. The study found a good number of hospital staff displayed clinically significant symptoms of post-traumatic distress, anxiety, depression, and burnout; moreover, hospital staff, particularly nurses and those working in intensive care units and COVID-19 sub-intensive wards, experienced a further increase in burnout and depression after 1 year [4]. The findings indicate the need to implement and test an intervention study aimed at mitigating the sustained psychological impact of the pandemic on those at greater risk of adverse psychological outcomes.

The present project proposed here aims to implement and evaluate the feasibility, acceptability, and effectiveness of a preliminarily tested intervention [32, 35] that integrates the most widely used and scientifically validated mindfulness protocols such as mindfulness-based stress reduction [19], mindfulness-based cognitive therapy [17, 20], and compassion-focused therapy [30], in a healthcare context (the Verona University Hospital Trust) during the COVID-19 pandemic. The purpose of the intervention is to reduce burnout and psychological distress amongst frontline nurses involved in the clinical management of COVID-19 patients.

## Methods

### Trial design

A randomized controlled trial (RCT) parallel group waiting list design will be used to assess the efficacy of a mindful and compassion programme for nurses (superiority trial) (Table 3 in Appendix). Participants will be randomly assigned to one of two groups: the experimental group will receive the Mindful Compassion Care Program (MCCP) [32, 35], and the control group will be allocated to a waiting list (WL) with an allocation ratio of 1:1. The effectiveness of the experimental intervention will be assessed by comparing the changes in the level of burnout at the end of the treatment and after 1-month later (this follow-up interval has been set due to organizational and time constraints). Other psychological dimensions will also be investigated (i.e. anxiety and depressive symptoms, posttraumatic symptoms, insomnia, perception of stress, mindfulness skills and evaluation of self-criticism and self-reassurance).

### Study setting

The study will be conducted at the Verona University Hospital Trust (Azienda Ospedaliera Universitaria Integrata [AOUI]), the second-largest hospital in Italy in terms of the number of beds and the fifth largest in terms of admissions. The trust employs 6000 people, including nearly 2000 nurses. On 17 March 2020, the Veneto regional government converted part of the hospital into a COVID-19 hospital. Dedicated pathways for both suspected and confirmed COVID-19 cases were established within the hospital, as well as in other hospital units located in clearly restricted areas devoted to the treatment of COVID-19 patients.

### Eligibility criteria

The population under investigation comprises frontline nurses who have been engaged over the two years of the pandemic in the clinical management of the most severe or critical COVID-19 cases (chief nurses and nurse managers will not be involved). Nurses will be recruited from intensive care units (ICUs) and sub-intensive COVID-19 wards (i.e. infectious disease unit, pulmonary medicine, internal medicine units converted to COVID-19 units). Eligible participants will be contacted by email by the research group and will receive an invitation to participate voluntarily.

To be included in the study, a participant/s will have to be (1) a nurse employed at AOUI for the past 2 years; (2) working within ICUs, infectious disease unit, and pulmonary medicine and internal medicine units that have been converted to COVID-19 sub-intensive units; and (3) scoring above the cut-off score for the Emotional Exhaustion sub-scale (EX) of the MBI-GS (equal to or greater than 2.20) in accordance with Italian norms [3].

Respondents will be excluded if they (1) have participated in mindfulness-based interventions in the previous 6 months; (2) show a score < 2.20 in the EX subscale of the MBI-GS; or (3) are receiving psychosocial or psychiatric treatment. Participants allocated to the WL will be requested not to participate in a mindfulness course offered elsewhere.

## Interventions

The MCCP comprises six regular 1 h and 30-min sessions and 1 all-day class lasting 4 h and 30 min. The intervention is a proven effective mindfulness programme [32, 35] based on well-known scientific programmes such as mindfulness-based stress reduction (MBSR) [19], mindfulness-based cognitive therapy (MBCT) [20] and compassion-focused therapy (CFT) [30]. It was pilot-tested in a non-randomized controlled trial of nursing students (*n* = 82) and exhibited medium to very large effect sizes (with Cohen’s *d* ranging from 0.57 to 1.25) in changes in burnout symptoms between both pre- and post-assessment in the experimental group, as well as control and experimental group in the post-assessment [32]. Two recent cases studies of nurses recruited during the pandemic showed reliable changes in several outcomes by the end of the intervention [35].

The MCCP consists of a theoretical component and standard mindfulness practices (i.e. mindfulness meditation exercises) along with a few bespoke practices. It aims to explain the foundations and the applications of a more mindful and compassionate approach to healthcare. It has three specific objectives: (a) to explore the concept of reflexivity as a tool in monitoring and revising nursing practice and illness experience, (b) to explain useful strategies that prevent burnout and promote engagement, and (c) to explain useful strategies that facilitate and foster compliance in patients [36]. The purpose of the intervention is to reformulate these general objectives through the lens and within the framework of mindful compassion.

The practice of mindfulness involves a series of formal exercises led by an experienced instructor. The participant will learn to bring their attention to the present moment through an awareness of their body, breathing, and senses; gradually relate to their inner and external experience in a more welcoming and non-judgmental way; and carry out informal exercises (e.g. they learn to extend to different moments in their day a the state of present-orientated awareness that they experience during their formal practices, e.g. by paying full attention to what they are doing at a certain point in time). Daily home practice is conducted through guided audio tracks and the completion and reading of a number of worksheets and materials.

Course activities will include mindfulness exercises led by an instructor that can be carried out every day, yoga practices with gentle body movements that are accessible to all, and group dialogue. Table 1 shows how the programme is to be structured.

**Table 1 Tab1:** Themes and programme of the MCCP

	Mindfulness exercises	Mindfulness psychoeducation
Week 1	Automatic pilot; soothing breath; standing yoga	Mindfulness practice and programmes; automatic pilot
Week 2	Automatic pilot: the day I suffered; soothing breath	Mind-wandering; thoughts and feelings
Week 3	Automatic pilot; experiential acceptance; standing yoga	Automatic thoughts; acceptance
Week 4	Soothing breath; compassionate self	Psychological flexibility; compassionate mind
Week 5	Sitting meditation; three pillars of death; mindful walking	Self-compassion; loving kindness
Week 6	Sitting meditation; loving kindness; compassion flowing out	Compassionate care
Final Session	Automatic pilot; sitting meditation; sitting yoga; breath meditation; mindful walking; loving kindness; compassion flowing in; compassion flowing out; breathing group	Summary

Exercises conducted during the intervention programme include a body exploration exercise, which consists of focusing the attention on different parts of the body (e.g. toes, back, and head) and physical sensations (e.g. pain or muscle tension) in the present moment; breath awareness meditation, which consists of turning the attention to the breath, noticing how bodily sensations change during inhalation and exhalation; and slow walking meditation, in which participants become aware of their steps, from beginning to end. Throughout, participants will be trained to maintain an attitude of acceptance, non-judgementalism, and equanimity, and foster attention, awareness, recognition, and emotional regulation. The mindful compassion sessions will allow participants to share their experience of practice or difficulties they have encountered. These will be followed by feedback from the teacher. The course will have a maximum of 12 participants.

If participants of either group report any adverse events during the trial, this will be registered in the electronic database system. Serious adverse events will be reported to the ethics committee. If participants require additional mental health support, they will be referred to the regular services, but it is also possible for participants to consult with an appointed psychologist if they so request or if the trainer so advises.

Each session will focus on topics that will be explored through specific exercises, presented by a licensed psychologists with demonstrated experience in the application of mindfulness-based protocols and who meets the criteria of the internationally agreed good practice guidelines of the UK network for mindfulness-based teachers.

If a given participant at the end of the trial continues to display high or higher levels of distress, they will be referred to the Psychiatric Consultation Service at the UOC of Psychosomatics, Verona Hospital Trust. This service has provided an individual help pathway for HCWs with psychological distress since the beginning of the pandemic. The WL is the control group planned for this study. It will remain in place for the entire period of the intervention. Details on the rationale of the study are shown in the flowchart (Fig. 1).

**Fig. 1 Fig1:**
[figure not shown]
Flowchart of the trial design

### Outcomes

As the proposed intervention aims to mitigate the prolonged strain on hospital staff by working with the most severe or critical COVID-19 patients, burnout—a specific indicator of chronic work-related dysfunctional response—was selected as the main outcome of interest. In particular, any change in the sub-subscale of emotional exhaustion (EX) between pre-treatment and 1-month post-treatment was chosen as the primary outcome of burnout [37]. Emotional exhaustion is a psychological construct that explores the perception of physical and emotional fatigue. It is characterized specifically by a lack of energy required to handle daily life and the prevalence of feelings of apathy and emotional detachment at work. It is the central dimension in burnout [38] and correlates strongly with job performance, absenteeism, higher psychopathological risk, and poor organizational effectiveness [39]. Numerous studies have found EX in HCWs to be associated with acute depressive symptoms, anxiety disorders, sleep problems, and poor quality relationships with patients [1, 33–35].

The secondary outcomes of the intervention will be to observe any change between pre-treatment and post-treatment and between pre-treatment and 1-month post-treatment, in:Professional efficacy (MBI-GS) [37]Cynicism (MBI-GS) [37]Depressive symptoms (PHQ-9) [40]Anxiety symptoms (GAD-7) [41]Post-traumatic symptoms (IES-R) [42]Insomnia (ISI) [43]Perception of stress (PSS) [44]Mindfulness skills (FFMQ) [45]Evaluation of self-criticism and self-reassurance (FSCRS) [46]

The assessment instruments to be used are as follows:Personal socio-demographic information will be collected by using an ad hoc schedule, addressing personal (gender, age, having had psychological problems developed before the COVID-19 outbreak, having received psychological treatment other than mindfulness over the past 2 years) and job-related characteristics (place of work within hospital, working experience, monthly night shifts).The Maslach Burnout Inventory–General Survey (MBI-GS) is a self-rated scale that explores the individual’s relationship with work with respect to burnout in particular. It is a modified and shortened version of the original MBI [37] and consists of 16 items and three subscales: emotional exhaustion (5 items), which measures feelings of being overextended and exhausted by one’s work; cynicism (5 items), which measures an indifference or a distant attitude towards your work; professional efficacy (6 items), which measures satisfaction with past and present accomplishments, and it explicitly assesses an individual’s expectations of continued effectiveness at work. Responses to the MBI-GS items are on a 6-point Likert scale, ranging from 0 (*never*) to 6 (*always*).Patient Health Questionnaire (PHQ-9) is a nine-question self-report measure of depression symptoms. It asks about the American Psychiatric Association’s Diagnostic and Statistical Manual (DSM) nine diagnostic symptoms of major depressive disorder and scores on each symptom range from 0 (*not at all*) to 3 (*nearly every day*) [40].Generalized Anxiety Disorder (GAD-7) is a self-rated questionnaire consisting of seven items that investigate the level of anxiety and worry felt by the respondent over the previous 2 weeks [41].Insomnia Severity Index (ISI) is a seven-item questionnaire that asks respondents to rate the nature and symptoms of their sleep problems [43].Impact of Events Scale – Revised version (IES-R) is a 22-item self-report that assesses subjective distress caused by traumatic events [42]. The IES-R contains seven additional items related to the hyperarousal symptoms of PTSD that were not included in the original IES. Respondents are asked to identify a specific stressful life event and indicate how distressed or bothered they had been during the previous 7 days according to each “difficulty” listed. Items are rated on a 5-point scale ranging from 0 (*not at all*) to 4 (*extremely*). The IES-R yields a total score (ranging from 0 to 88). Subscale scores can be calculated for the intrusion, avoidance, and hyperarousal subscales.Perceived Stress Scale (PSS) is a 10-item questionnaire to measure the degree to which life situations are appraised as stressful. Psychological stress has been defined as the extent to which persons perceive (or appraise) that demands upon them exceed their ability to cope [44].The Five Facet Mindfulness Questionnaire (FFMQ) is a self-report measure consisting of 39 items based on a five-facet model (i.e. observe, describe, act with awareness, nonjudgement, and nonreaction) [45]. It is widely used for dispositional mindfulness [14].Forms of Self-Criticising/attacking and Self-Reassuring Scale (FSCRS) is a self-administered tool for the assessment of three forms of self-to-self relating as a process measure [46]. Two subscales represent maladaptive forms of self-to-self relating, namely, self-criticism induced by the desire to correct or improve certain aspects of the self—which is referred to as inadequate self (IS)—and self-criticism arising from the desire to hurt, persecute, and attack the self—which is referred to as hated self (HS). A third subscale, RS, reflects the ability to reassure oneself. The questionnaire consists of 22 items.

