**Assessments**					
Burnout			X	X	X
Depression symptoms			X	X	X
Anxiety symptoms			X	X	X
Post-traumatic symptoms			X	X	X
Insomnia			X	X	X
Perception of stress			X	X	X
Mindfulness skills			X	X	X
Self-criticism and self-reassurance			X	X	X

Primary and secondary outcomes will be measured at baseline (T1), at the end of the intervention (T2), and 1 month after the end of intervention (T3). Adverse events and untoward effects will be assessed during each treatment. Table 1 contains a summary of all the measures in the trial.

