### Statistical methods

Statistical analysis will be based on an intention-to-treat (ITT) basis, comparing outcomes from all nurses allocated to the two trial arms. Findings will be reported according to the CONSORT guidelines for parallel-group randomized trials [47].

Personal socio-demographic information and job-related characteristics will be summarized descriptively according to the treatment arms. Categorical data will be presented as frequencies and percentages. Means, standard deviations, medians, interquartile ranges, and minima and maxima will be presented for continuous data. To verify the success of randomization, the baseline characteristics of the two treatment groups will be compared: continuous variables will be compared with a *t*-test (for normally distributed variables) or the Mann-Whitney *U* test (for non-normally distributed variables). Categorical variables will be evaluated with the chi-square or 2-tailed Fisher exact test. Change scores will be calculated. Data will be presented as percentages for categorical data and means and standard deviations for continuous data; 95% CIs will be used to indicate uncertainty around the estimates.

Follow-up data will be analysed using mixed models to establish the correlation between repeated measurements and examine main effects and their interaction, adjusting for the baseline score. The presence of multi-collinearity, interaction, and higher power terms will be assessed to check final model validity. Statistical significance will be defined at two-sided *p* < .05. All analyses will be carried out using Stata 17.0 for Windows.

The effects of baseline covariates expected to have an important influence on the primary outcome will be controlled for by comparing covariate-adjusted analyses with unadjusted analyses. Certain covariates that will be considered at baseline will refer to demographic variables (e.g. gender, age, and education level), the organizational context, and participation in non-mindfulness support courses.

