Target sample size	72
Recruitment status	Advertising
Primary outcome(s)	Change in the sub-subscale of emotional exhaustion (EX) of the Maslach Burnout Inventory-General Survey (MBI-GS) between pre-treatment and post-treatment
Key secondary outcomes	Change between pre-treatment and post-treatment on the following dimensions: - Professional efficacy (MBI-GS) - Cynicism (MBI-GS) - Depressive symptoms (PHQ-9) - Anxiety symptoms (GAD-7) - Post-traumatic symptoms (IES-R) - Insomnia (ISI) - Perception of stress (PSS) - Mindfulness skills (FFMQ) - Evaluation of self-criticism and self-reassurance (FSCRS)

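### The primary endpoint is set at two different visits: one month after treatment in the Outcomes section, end of treatment in the registration data set

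*Protocol article*

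**What the plan says.** - **Outcomes.** The primary outcome is the change in EX to one month after treatment: "any change in the sub-subscale of emotional exhaustion (EX) between pre-treatment and 1-month post-treatment was chosen as the primary outcome of burnout". The secondary outcomes are to be read over two intervals: "any change between pre-treatment and post-treatment and between pre-treatment and 1-month post-treatment".
- **Appendix, Table 3 (registration data set).** The primary outcome is "Change in the sub-subscale of emotional exhaustion (EX) of the Maslach Burnout Inventory-General Survey (MBI-GS) between pre-treatment and post-treatment". The key secondary outcomes are likewise given only from pre-treatment to post-treatment, so the one-month visit appears in no outcome in this table.
- **Trial design.** Effectiveness is to be assessed by "comparing the changes in the level of burnout at the end of the treatment and after 1-month later". Neither visit is ranked above the other.
- **Participant timeline, Table 2.** Post-treatment (T2) and follow-up (T3) have separate columns, and burnout is assessed at both. The text below the table defines T2 as the end of the intervention and T3 as one month later.
- **Sample size.** 36 nurses per arm for a mean difference of −1.21 with SD 1.8, 80% power, two-sided 0.05. The calculation refers to the primary outcome but names no visit.
- **Statistical methods.** Mixed models on the follow-up data will "examine main effects and their interaction, adjusting for the baseline score", with significance at two-sided p < .05. No visit is named for the primary contrast.

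**The concern.** T2 and T3 answer different questions. T2 asks whether EX is lower when the course ends; T3 asks whether a difference is still there a month later. The two results can disagree, and each would have a statement in the article calling it the primary outcome.

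Two things are at stake. First, the published primary result could differ from the listed one without anyone being able to say from the protocol which was intended. Second, if the choice is made after the data are seen, the 5% level no longer describes the chance of a false primary claim. It matters more here because EX is self-rated and participants are not blinded, so firm advance definition is one of the few protections the trial has.

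**Working it through.** **1. Is it one visit under two names?** No. The Outcomes section lists the two intervals separately for the secondary outcomes, Table 2 gives T2 and T3 separate columns, and the text below it defines them a month apart. Table 3 is current text, an appendix cited from Trial design, not a record of superseded wording. It also gives the secondary outcomes at T2 only, so it cannot be read as shorthand for the Outcomes section.

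**2. Does another section settle it?** Trial design names both visits. Sample size and Statistical methods name neither, and give no testing order or split of the significance level.

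**3. Reproduce the stated sample size.** Inputs from Sample size: difference 1.21, SD 1.8, n = 36 per arm, two-sided α = 0.05.

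- Noncentrality = 1.21 / (1.8 × √(2/36)) = 2.85, with 70 degrees of freedom.
- Noncentral t power: 0.803 at 36 per arm and 0.792 at 35. So 36 is the smallest n per arm that reaches 80%.
- The calculation assumes one test at 0.05 and reproduces on that basis.

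**4. Error rate if either visit were allowed to count.** Under no effect, let Z2 and Z3 be the test statistics at T2 and T3, bivariate normal with correlation r. The documents do not give r, so a range is shown.

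- Any significant result: 1 − P(|Z2| ≤ 1.96 and |Z3| ≤ 1.96)
- Only results favouring the intervention: 1 − P(Z2 ≤ 1.96 and Z3 ≤ 1.96), taking positive Z as benefit

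| r (assumed) | Two-sided, nominal 5% | Favouring intervention, nominal 2.5% |
|---|---|---|
| 0 (upper bound) | 9.75% | 4.9% |
| 0.5 | 9.1% | 4.5% |
| 0.7 | 8.3% | 4.2% |
| 0.8 | 7.8% | 3.9% |
| 0.9 | 7.0% | 3.5% |

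Check at r = 0: 1 − 0.95² = 0.0975.

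**5. What each way out costs.**

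- One named visit: n = 36 per arm, α = 0.05, power 80.3%.
- Both visits as alternative primaries with α split to 0.025 each: power per visit falls to 71.2% at 36 per arm. Reaching 80% needs 44 per arm, 88 in total.

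**The case against.** The best defence is that the Outcomes section is clear on its own: it says one month was chosen, and Table 3 is a summary. That does not remove the problem. Table 3 is the registration data set, with registration dated 1 April 2022, before the September 2022 start, and its entry is just as definite.

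Three narrower objections stand.

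- **Trial design is not a third definition.** A reader might count it as one. It speaks of the level of burnout, and uses neither the word primary nor the name of the EX subscale. It is compatible with EX at T3 as primary and the other burnout subscales as secondary at both visits. It is unranked wording; the contradiction is between Outcomes and Table 3.
- **No either-visit rule is written down.** A reader might infer that the plan lets success be claimed at whichever visit is favourable, and so runs at 8% or 9% error. The documents do not support that: Outcomes and Table 3 each name a single visit. The rates above describe what could follow from leaving the choice open, at correlations that are assumed. The two-sided figures also count results that favour the waiting list; for a false claim of benefit, the right-hand column is the relevant one.
- **The documents do not prove that T3 was intended throughout.** Only the Outcomes section points to it, and the sample size names no visit. Moving Table 3 to T3 changes a listed primary outcome; it is more than an edit of wording.

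**Conclusion.** The point holds as an internal contradiction about the primary endpoint: EX change to T3 in Outcomes, EX change to T2 in Table 3, with nothing elsewhere to decide between them. A second, smaller mismatch goes with it: the secondary outcomes are at T2 and T3 in Outcomes but at T2 only in Table 3.

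The size is conditional. If significance at either visit were accepted, the two-sided error would be about 9.1% to 7.0% for r from 0.5 to 0.9, or 4.5% to 3.5% against 2.5% for results favouring the intervention. This assumes bivariate normal test statistics and correlations that the documents do not give. It is not an error rate that the plan itself sets.

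Either visit would be a legitimate primary time point, and the sample size is not in error. Even so, this must be fixed, because the trial's main result is undetermined until one visit is named.

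**What to change.** Before outcome data are seen:

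1. Name one visit as the single primary time point for EX, and make EX at the other visit a secondary outcome. T3 is the one that the Outcomes section explicitly chose.
2. Make Trial design, Outcomes and Table 3 agree, with Trial design saying which visit is primary.
3. If this changes the registered primary outcome, record the change with its date and reason.
4. In Statistical methods, state that the primary test is the between-group EX contrast at the named visit, from the mixed model, at two-sided 0.05.
5. Align the secondary time points in Table 3 with those in Outcomes (T2 and T3).

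The cost is edits to Trial design, Statistical methods and Table 3 (and to Outcomes, so that EX at the other visit is listed as secondary), plus a registry update if the listed outcome changes. No further participants or assessments are needed: 72 nurses still give 80.3% power for one test at 0.05. Keeping both visits as alternative primaries would need an explicit multiplicity rule; with an equal split of the significance level it would take 88 nurses to hold 80% power at each visit.
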